### Primary analyses

The primary analyses will evaluate the effects of the intervention on parent and child outcomes. These analyses will include reports obtained from parents who were the primary receivers of the intervention as well as reports on child’s illness severity and observational assessment. A multilevel modeling approach will be used to take into account the repeated measurements and thus non-independence of observations [66]. Dummy codes contrasting the groups will serve as fixed effects, allowing for random intercepts and slopes to vary across individuals. Significant fixed effects contrasting INT with CAU will indicate whether the intervention is an improvement over usual care. Separate models will be estimated for each outcome measure using Bonferroni correction to control for inflation of Type 1 error due to multiple comparisons.

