## Aims and hypotheses

This study aims to use multi-informant assessment to test the efficacy of *Positive Parenting for Healthy Living* for parents of children with type 1 diabetes. Specifically, the primary outcomes will be: (i) parent self-reported parenting behaviour; (ii) child-reported parenting behaviour; (iii) parent-reported child behaviour and adjustment; and (iv) parent-reported child health-related quality-of-life. Secondary outcomes will be: (i) child’s metabolic control (as indicated by HbA1c and within-range blood glucose readings); (ii) parents’ self-efficacy with diabetes management; (iii) parent-reported illness-specific child behaviour problems; (iv) parent-reported family quality-of-life; (v) parents’ diabetes-related stress and (vi) general parenting stress; (vii) observed parenting behaviour; and (viii) observed child behaviour. We hypothesise that, compared to a CAU group, the intervention group (INT) will show significantly greater improvement on each outcome measure at (a) post-intervention and (b) 6-month follow-up.

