### Sample size and power analysis

The required sample size for the study was calculated to assure 80 % power to detect an effect size of ES = .5 for a mean difference in rates of change in the variables of interest between the groups (INT vs CAU and/or mother vs father vs child). This effect size is categorized as medium based on Cohen’s guidelines and has been chosen based on our previous research [35]. In multilevel models with repeated measures, the sample size is effectively the number of observations (the level-1), not number of participants (level-2 units). We performed power analysis using G*Power software [69] for rANOVA, looking at the within-between interactions and allowing for conservative estimate of intra-individual variability (.5). The analyses indicated that a sample size of 50 is sufficient to detect an ES of .5 at the significance level of .05 (two-tailed). This is without taking into account the added power accorded by the rich repeated measures in our data. Assuming 16 % attrition rate, an available sample of 60 families will be sufficient to detect medium sized effects.

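### The 80% power is stated at .05, but the INT vs CAU outcome tests are Bonferroni-corrected over an undefined family that reaches into secondary outcomes

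*Protocol article*

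**What the plan says.** All references are to the protocol article.

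- **Sample size and power analysis.** The target is set as follows: "The required sample size for the study was calculated to assure 80 % power to detect an effect size of ES = .5". The conclusion is that "a sample size of 50 is sufficient to detect an ES of .5 at the significance level of .05 (two-tailed"). The section does not mention multiple testing. The effect is described only by a label: "This effect size is categorized as medium based on Cohen’s guidelines". The method is G*Power "for rANOVA, looking at the within-between interactions and allowing for conservative estimate of intra-individual variability (.5"). The power statement covers differences "between the groups (INT vs CAU and/or mother vs father vs child"). Allowing for 16% attrition, 50 becomes 60 families.
- **Primary analyses.** The multiplicity rule is: "Separate models will be estimated for each outcome measure using Bonferroni correction to control for inflation of Type 1 error". The data covered are reports from the parents who received the intervention, "as well as reports on child’s illness severity and observational assessment". Neither the number of tests nor the corrected threshold is given.
- **Aims and hypotheses.** Four primary outcomes are listed: parent-reported parenting, child-reported parenting, child behaviour and adjustment, and child quality of life. Eight secondary outcomes follow, among them metabolic control (i), observed parenting (vii) and observed child behaviour (viii). The hypothesis is that the intervention group "will show significantly greater improvement on each outcome measure at (a) post-intervention and (b) 6-month follow-up".
- **Secondary analysis.** Dyad and triad models are described, with no correction stated.

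**The concern.** Two statements about the same tests do not fit together. The trial is sized at one significance level, and its outcome models are to be judged at a smaller one. Four primary outcomes alone put the Bonferroni threshold at .05/4 = .0125, and any wider family lowers it further.

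The family is also badly fixed. The section that sets the correction brings in outcomes that the aims call secondary, and it speaks of each outcome measure without limit. Read as written, HbA1c, glucose readings and observed behaviour can share the alpha that should protect the primary outcomes. With no divisor on record, the threshold could be settled after the data are seen. A null result on a primary outcome also could not be read against the claimed 80%.

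**Working it through.** **1. Inputs.** From the sample size section: alpha .05 two-tailed, power 80%, ES .5 called medium, within-between interaction, .5 for intra-individual variability (read here as the correlation among repeated measures), N = 50 complete. From the Design section: 2 groups × 3 times, 1:1. From the aims: 4 primary and 8 secondary outcomes, 2 hypothesised time points.

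**2. The plan's own figure.** The G*Power within-between formula is λ = f²·N·m/(1 − ρ), with df (k − 1)(m − 1) and (N − k)(m − 1). A medium effect of d = .5 corresponds to f = .25. With k = 2, m = 3, ρ = .5:

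- N = 28: λ = .0625 × 28 × 3/.5 = 10.5, power 81%. So 28 families are enough for 80%.
- N = 50: λ = .0625 × 50 × 3/.5 = 18.75, power 97.6%.

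The figure of 50 is not reproduced from the stated inputs. Other settings do not give it either: two time points give 34, zero correlation gives 54, f = .5 gives 10, and a two-sample t-test of d = .5 gives 128. The nearest is six cells (arm × informant) over three times. That has 82% power at 50 but needs 54 in equal cells, and it treats family members as independent. The attrition step does reproduce: 50/(1 − .16) = 59.5, rounded up to 60.

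**3. Candidate divisors.** The document states none, so these are assumptions:

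- 4: the primary outcomes.
- 12: all listed outcomes, 4 + 8.
- 30: every primary score at both time points. The scores are APQ parent 4 + APQ child 5 + CAPES 3 + PedsQL 3 = 15, and 15 × 2 = 30.

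**4. Power at N = 50 under three readings of the effect size.**

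| Tests | Alpha | (a) 50 gives exactly 80% at .05 | (b) Literal 2×3, f = .25, ρ = .5 | (c) Plain two-group d = .5, 25 per arm |
|---|---|---|---|---|
| 1 | .05 | 80% | 97.6% | 41% |
| 4 | .0125 | 61% | 92% | 22% |
| 12 | .0042 | 45–47% | 85% | 12% |
| 30 | .0017 | 33–35% | 77% | 7% |

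Column (a) takes the effect that has 80% power at .05 and tests it at .05/k. The two-sample form (d = .809) gives the lower value and the 2×3 interaction form the higher. A normal approximation agrees closely: Φ(1.960 + 0.842 − 2.498) = Φ(0.304) = 62% for 4 tests. Column (c) uses the two-sample noncentral t.

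**5. Sample size implied by reading (a).** For 4 tests, N = 50 × [(2.498 + 0.842)/(1.960 + 0.842)]² = 71.04, so 72 complete, and 72/.84 = 85.7, so 86 enrolled. For 12 tests, N = 50 × [(2.865 + 0.842)/2.802]² = 87.5, so 88 complete, and 88/.84 = 104.8, so 105 enrolled. The plan enrols 60.

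**The case against.** Several points can fairly be made for the plan.

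- **Not every test is affected.** A reader might infer that the stated power applies to no test in the trial. The documents do not support that. The dyad and triad models carry no stated correction, and the power statement names the mother, father and child comparison. The mismatch is confined to the corrected INT vs CAU models.
- **No divisor of 12 is written.** A reader might take 12 as the rule, since the hypothesis covers each outcome measure. That is a reasonable reading but not a stated one. The data listed under Primary analyses do not name child-reported parenting, which would make 11. Counting subscales or time points separately is a further assumption, because the section describes one model per measure.
- **Under-power is not shown.** A reader might conclude that the trial is too small. On the literal G*Power reading, power stays at or above 80% for up to about 20 tests (80.7% at .0025). The article calls 50 sufficient, not minimal. All randomised families are analysed by full information maximum likelihood, so partial data from those who drop out also contribute.
- **The lowest figures are not due to Bonferroni alone.** For a plain d = .5, 80 − 41 = 39 of the 58 points between 80% and 22% are lost before any correction, and 41 − 22 = 19 come from dividing by 4.
- **A wide Bonferroni family is conservative,** so the false-positive risk is not raised.

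These points limit the size of the claim. They do not remove the mismatch between two statements in the same article, or the inclusion of secondary outcomes under the corrected primary analyses. The literal reading does not rescue the power section either: it needs only 28 families, so it is not the calculation that produced 50.

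**Conclusion.** The point holds in limited form. The 80% at .05 is not the power of any Bonferroni-corrected INT vs CAU test, and as written the corrected set can include secondary outcomes at the expense of the four primary ones.

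The loss cannot be fixed at one number, because both the divisor and the effect size metric are undefined. At a divisor of 4, power at N = 50 is about 61% if 50 is the true minimum at .05, 92% on the literal G*Power reading, and 22% for a plain two-group d = .5. These values assume 50 complete families in equal arms and, for the literal reading, that .5 is the correlation among repeated measures. What is established is a power figure tied to a threshold the corrected tests will not use, not that the trial is under-powered.

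**What to change.** **In Primary analyses:** confine the corrected family to the primary outcomes and state how many tests it contains, including how the two time points are counted. Replace Bonferroni with Holm, which gives the same family-wise control and is never less powerful. Report illness control, observed behaviour and the other secondary outcomes outside this family as supportive.

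**In Sample size and power analysis:** say whether ES is d or f, give the G*Power options used, and restate power at the corrected alpha for the planned 60 families (50 complete).

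Naming one score per instrument, or leaving out low-reliability subscales, would shorten the family. Those are design preferences rather than corrections of an error.

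**Cost:** wording in two sections. Secondary outcomes lose confirmatory status, and the stated power may fall.

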### Secondary analysis

The secondary analysis will take advantage of the multiple-informant design of the study. We will investigate if the effects of the intervention are the same for parents who attended the intervention as opposed to their partners or their children, with respect to parenting practices, child adjustment, parental self-efficacy (general and diabetes management related), family quality of life and parental stress. We will apply a multilevel modeling approach adopted for dyads (mother and father) or triads (mother, father, and child) [67, 68] to model change in outcome variables for mothers, fathers and children individually while accounting for similarities within dyads or triads. We will investigate whether the intervention is beneficial for both parents, or has different effects for a parent who participated in the intervention as opposed to one that didn’t. Further, we will examine if the changes in parenting practices are the same as reported by mother, father and the child. Finally, we will evaluate whether the intervention has an effect on the family as a whole, such as decreasing discrepancies between mothers and fathers.

### Sample size and power analysis

The required sample size for the study was calculated to assure 80 % power to detect an effect size of ES = .5 for a mean difference in rates of change in the variables of interest between the groups (INT vs CAU and/or mother vs father vs child). This effect size is categorized as medium based on Cohen’s guidelines and has been chosen based on our previous research [35]. In multilevel models with repeated measures, the sample size is effectively the number of observations (the level-1), not number of participants (level-2 units). We performed power analysis using G*Power software [69] for rANOVA, looking at the within-between interactions and allowing for conservative estimate of intra-individual variability (.5). The analyses indicated that a sample size of 50 is sufficient to detect an ES of .5 at the significance level of .05 (two-tailed). This is without taking into account the added power accorded by the rich repeated measures in our data. Assuming 16 % attrition rate, an available sample of 60 families will be sufficient to detect medium sized effects.

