### Participants

Participants will be 60 families of 2–10 year old children with type 1 diabetes, recruited through primary care settings, paediatric specialists, specialist clinics at major Brisbane hospitals, and through targeted mail-out and media campaigns. Diagnostic confirmation of the child’s diabetes will be sought from the child’s treating diabetes team.

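### The stated 80% power for a medium effect with 50 families is not reached: at correlation .5 a .5 SD difference between arms has about 41–52% power, and at most about 69%

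*Protocol article*

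**What the plan says.** All of this is in the protocol article, mainly under Sample size and power analysis.

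- **Target.** The sample size was "calculated to assure 80 % power to detect an effect size of ES = .5". The effect is defined as "ES = .5 for a mean difference in rates of change in the variables of interest between the groups", meaning intervention (INT) versus care as usual (CAU) and/or mother versus father versus child. On its size: "This effect size is categorized as medium based on Cohen’s guidelines".
- **Method.** G*Power, repeated-measures ANOVA, within-between interaction, with .5 entered for intra-individual variability and described as conservative. The article does not say whether the effect entered was d or f, how many groups and measurements were used, or which effect-size option was chosen.
- **Result.** "a sample size of 50 is sufficient to detect an ES of .5 at the significance level of .05 (two-tailed"). With 16% attrition this becomes 60, and the Participants section confirms the unit: "Participants will be 60 families of 2–10 year old children with type 1 diabetes".
- **Supporting statements.** In multilevel models with repeated measures, "the sample size is effectively the number of observations (the level-1), not number of participants (level-2 units"). After the figure of 50 the article adds: "This is without taking into account the added power accorded by the rich repeated measures in our data".
- **Planned analysis.** The Primary analyses section specifies multilevel models with random intercepts and slopes, one per outcome, with Bonferroni correction. The Design section gives two arms, three time points and 1:1 allocation.

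**The concern.** A mean difference of .5 described as medium by Cohen's guidelines is the d scale. G*Power's interaction test takes f, for which medium is .25 and .5 lies above large (.40). Two arms of 25 would not ordinarily give 80% power for a .5 SD difference, so the stated figure needed checking.

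The two supporting sentences make the figure look safer than it is. Arm is allocated to families, so repeated observations on a family cannot serve as independent units for the INT–CAU contrast. A within-between repeated-measures calculation would also normally include the repeated measures already.

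What is at stake is interpretation. If the trial reports 80% power for medium effects, a null result will be read as evidence against a medium effect. With the stated inputs, the chance of detecting one may have been below one half.

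**Working it through.** **Inputs.** Two-sided alpha .05, power 80%, effect .5, N = 50 before attrition and 16% attrition come from the sample-size section. Two arms, three waves and 1:1 allocation (25 per arm) come from Design. The .5 for intra-individual variability is read as the correlation ρ between repeated measures; that reading is an assumption.

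**1. The plan's own figure.** The attrition step reproduces: 50/0.84 = 59.5, so 60. For the 50, G*Power's default option uses λ = f²·N·m/(1−ρ), with df (k−1)(m−1) and (N−k)(m−1), for k groups and m waves. At ρ = .5:

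| f | groups | waves | N for 80% |
|---|---|---|---|
| .50 | 2 | 3 | 10 |
| .50 | 2 | 2 | 12 |
| .25 | 2 | 3 | 28 (λ = .0625·28·3/.5 = 10.5; power 81%) |
| .25 | 2 | 2 | 34 (λ = .0625·34·2/.5 = 8.5; power 81%) |
| .25 | 6 | 3 | 49 (λ = .0625·49·3/.5 = 18.4; power 81%) |

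No two-group version in this table gives 50. The six-group version (two arms by three informants) gives 49, or 54 if the six groups must be equal.

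**2. Power for a .5 SD INT–CAU difference, 25 families per arm, ρ = .5.** Outcome SD is set to 1, and noncentrality is (.5/SD)·√(25/2).

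- Pre–post change: SD = √(2(1−.5)) = 1; noncentrality 1.77 on 48 df; **power 41.0%**. For 80%, 64 per arm (128 families) would be needed.
- Interaction in the 2 × 3 design, with the difference 0, .5, .5 over the waves: the centred sum of squares is 1/9 + 1/36 + 1/36 = .167, so f = √(.167/12) = .118. λ = (50/4)·.167/.5 = 4.17 on 2 and 96 df; **power 41.9%**. For 80%, 118 families would be needed.
- Baseline-adjusted, one time point: SD = √(1−.25) = .866; noncentrality 2.04; **power 51.6%**.
- Baseline-adjusted mean of both follow-ups: SD = √(.75−.25) = .707; noncentrality 2.50; **power 68.8%**. With all 60 families retained, noncentrality is .707·√15 = 2.74 and power is 76.8%.

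**3. Sensitivity to the correlation** (N = 50, effect in SDs of the outcome):

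| ρ | change | baseline-adjusted, one time point |
|---|---|---|
| .3 | 31% | 44% |
| .5 | 41% | 52% |
| .7 | 61% | 68% |
| .8 | 78% | 82% |

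The adjusted mean of both follow-ups reaches 82% at ρ = .7. If the .5 is instead in SDs of the change score, power on change is 41% whatever the correlation.

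**4. Difference detectable with 80% power** (N = 50, ρ = .5, alpha .05): about .81 SD on pre–post change, .70 SD baseline-adjusted at one time point, and .57 SD for the adjusted mean of both follow-ups.

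**5. Planned alpha.** The calculation uses .05, but the analysis applies Bonferroni. Taking four primary domains as an illustration, .05/4 = .0125. Baseline-adjusted power at one time point is then about 60% for .7 SD and about 30% for .5 SD.

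**6. Unit.** The level-1 sentence counts observations, yet the 50 is inflated to 60 families as though it counted families. The two statements do not fit together.

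**The case against.** **Cause.** A reader might infer that the team entered d where G*Power wants f, or counted observations as families, and that this produced the 50. The documents do not support that. With two groups neither f = .5 nor f = .25 gives 50 in the default option. The mother/father/child target in the same section makes a six-group calculation with f = .25 plausible, and that gives 49. It does not rescue the claim, since 80% power for that interaction is not 80% power for a .5 SD difference between two arms, and the 50 would then not count families.

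**Supporting sentences.** The same section also powers comparisons within families, where observations below family level do carry information. The level-1 sentence is therefore wrong for the arm effect but not for every contrast. Calling the added-power sentence double counting assumes how many waves were entered, which is not stated.

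**Correlation and missing data.** The .5 is called conservative, so the team may expect better. The full-information likelihood analysis under Missing outcome data uses all randomised families, so 69% is a ceiling only for 50 families at ρ = .5. Both points stand. Even so, 60 fully retained families reach only 77% at ρ = .5, and the article states no higher correlation.

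**A condensed article.** Unstated inputs could be left to a fuller document. The objection here is to a stated power figure, not to an omission.

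**Conclusion.** The concern holds in this form: the stated 80% power for a medium difference of .5 between arms is not delivered by 50 families on the article's own inputs. Power is about 41–42% on change, 52% baseline-adjusted at one time point, and at most 69% using both follow-ups (77% with no loss from 60). This assumes that .5 is a standardised mean difference, that the stated .5 is the correlation, equal arms, and alpha .05. The planned Bonferroni correction lowers power further.

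The level-1 statement is wrong for a treatment allocated to families. The origin of the 50 remains undetermined: if .5 was f, medium is the wrong label; if it was d, 50 is not sufficient.

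A reader might also infer that the trial must double in size. That does not follow. The 118–128 families belong to the less efficient change analyses at ρ = .5, and what needs correcting is the power claim.

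**What to change.** Revise the sample-size section as follows.

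1. Delete the level-1 sentence, or limit it to within-family contrasts, and say that the INT–CAU comparison is limited by the number of families.
2. Delete the added-power sentence unless the calculation is shown to have left out the repeated measures.
3. State the effect metric (SD units of the INT–CAU difference at a named time point), the number of groups and waves, and the correlation assumed.
4. Replace the closing claim about medium-sized effects with the power and detectable difference for the planned INT–CAU multilevel model at the planned Bonferroni-adjusted alpha.

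The baseline-adjusted, single-time-point figures (.70 SD at 80% power with alpha .05; about 60% for .7 SD and 30% for .5 SD at .05/4) are a guide to scale. They should not be pasted in, because that is not the planned model.

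The cost is one recalculation and some rewording. Enrolment, outcomes and analysis stay as they are, but the stated power becomes less favourable.

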### Missing outcome data

In any longitudinal design it is inevitable that some individuals will drop out from the study. For this reason, the study sample size was calculated to allow for a dropout rate of 16 %. Assuming that the complete data may only be available for 84 % of families at the end of the study, intention-to-treat analysis will be applied to allow all randomized families to be included in the analyses. Missing data will be accommodated via implementation of full information maximum likelihood analysis (FIML). This approach yields intention-to-treat estimates consistent with what would be expected if there were no missing data, given that the assumptions of either Missing Completely at Random (MCAR) or Missing at Random (MAR) are met [65].

